## Design

RadTARGET is a phase II, two-arm, randomized clinical trial evaluating tumor-focused RT versus standard-dose RT. Evaluation will be performed in terms of physician-reported adverse events, patient-reported safety, and oncologic outcomes. Participants will undergo RT for intermediate- or high-risk localized PC (Fig. 1). A dynamic allocation procedure is used to assign participants in a 1:1 ratio to receive either standard-dose RT or image-guided, tumor-focused RT. To minimize biased clinical decision-making based on randomization, treating physicians will declare the participant’s treatment plan prior to randomization. Each arm will be balanced for risk group (intermediate/high), fractionation type (stereotactic body RT [SBRT] / non-SBRT), duration of androgen deprivation therapy (ADT; none/short-term/long-term), bladder filling (full/empty), and spacer use (yes/no). The primary objective is to evaluate the relative merits of image-guided, tumor-focused RT vs. standard-dose RT for acute GU/GI adverse events in the setting of definitive RT for intermediate- and high-risk PC. The endpoint will be acute, any-attribution GU/GI grade ≥2 adverse events within 3 months of completing RT, compared between randomized arms. Adverse events will be defined using Common Terminology Criteria for Adverse Events (CTCAE) version 5.0 grading.

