### Statistical analysis

We adopt a statistical approach based on estimating the difference in adverse event rate (proportion of patients experiencing an adverse event) between the two randomized groups by controlling the precision (width) of the associated confidence interval for that difference. The primary endpoint is acute GU or GI grade ≥2 adverse events. We will estimate the absolute difference in adverse event rate between tumor-focused radiotherapy and standard dose radiotherapy using an intention-to-treat (ITT) analysis approach.

The following randomized trials and meta-analyses guide our assumptions for sample size determinations: RTOG 0415, PROFIT, HYPRO, PACE-B, FLAME, Hypo-FLAME, and MIRAGE [2], [4], [13], [27], [28], [29], [30]. From this high-level evidence, we assume the combined GU and/or GI acute adverse event rate is 40%. The MIRAGE trial included 156 participants and found a meaningful difference in acute GU and GI safety when comparing a difference in PTV margin size of 2 mm. We assume that the tumor-focused approach will lead to a similar adverse event reduction via the same mechanism.

We seek to answer whether the tumor-targeted approach reduces the rate of acute GU/GI adverse events. If we assume acute adverse events are reduced from 40% to 25% (absolute rate difference of −15%), we estimate that a sample size of 150 participants (75 in each arm) will yield a one-sided 90% confidence interval (one-sided equivalent to 95% confidence interval for a two-sided test) with 12.4% margin of error. Thus, we expect to have >95% confidence that the true rate difference is non-zero. We expect minimal attrition, but even 10% missing data would have a minimal impact on the margin of error (<1%). If adverse event rates in the standard arm were higher or lower than expected (30–70%), we would still have sufficient power to detect the assumed 15% absolute rate difference.

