All primary and secondary analyses will be conducted with the intention-to-treat principle. All participants will be analyzed according to the group they were randomly assigned to, regardless of compliance with the trial protocol. Patients who did not receive RT treatment will be considered screen failures. The primary endpoints (proportion of patients with acute grade ≥2 GU or GI adverse events) will be compared across the two randomized groups using a stratified Cochran–Mantel–Haenszel test with the stratification factors listed above. We will also repeat the analysis using a non-stratified Fisher’s exact test.

Secondarily, we will develop a multivariable logistic regression model with binary dependent variable (presence or absence of acute grade ≥2 GU or GI adverse events) and independent variables to include randomization group and all covariates listed above. This will allow us to estimate the effects of each variable, with bootstrap 95% confidence intervals. The primary and secondary analyses above will be repeated in the following subgroups: (1) self-reported race/ethnicity, and (2) age <65 vs. ≥65 years. This is in addition to subgroup analyses within the stratification groupings for randomization. Description of translational sub-studies provided in the Supplement.

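### The screen-failure rule is not limited to patients not yet randomized, so it contradicts the promised ITT analysis and permits post-randomization exclusions that can differ by arm

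*Protocol article*

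**What the plan says.** In the protocol article, Statistical analysis, the governing statement is "All primary and secondary analyses will be conducted with the intention-to-treat principle". It is followed by "All participants will be analyzed according to the group they were randomly assigned to, regardless of compliance with the trial protocol". The sentence after that reads "Patients who did not receive RT treatment will be considered screen failures". The same section also names ITT as the approach for estimating the primary difference.

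The Design section fixes the order of events. To limit biased decisions, "treating physicians will declare the participant’s treatment plan prior to randomization". A dynamic procedure is then used to "assign participants in a 1:1 ratio to receive either standard-dose RT or image-guided, tumor-focused RT". The primary endpoint is "acute, any-attribution GU/GI grade ≥2 adverse events within 3 months of completing RT, compared between randomized arms", so its window is anchored on finishing radiotherapy.

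**The concern.** Not receiving the assigned radiotherapy at all is the most complete form of non-compliance. One sentence keeps such a patient in the assigned arm and the next takes the patient out. For a randomized, untreated patient the two cannot both apply.

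Whether radiotherapy was received is known only after randomization. The treating physician must know the allocation in order to contour and plan, because the target volumes and doses differ between the arms (Experimental arm; Control arm). The Design section itself recognizes that knowledge of the allocation could bias clinical decisions. Exclusion on a post-randomization event, in the hands of someone who knows the arm, is the situation ITT is meant to guard against. At stake is the estimated difference in the primary endpoint, and the label under which it is reported. That result is to decide whether a phase III trial is warranted (Summary).

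**Working it through.** **Step 1: the text.** The ITT sentence covers all participants by randomized group, regardless of compliance. The screen-failure sentence covers patients without radiotherapy and sets no time limit. Eligibility (Table 1) asks for a plan for curative-intent radiotherapy, not its receipt. The plan is declared, then the patient is randomized, then treated. A randomized patient can therefore meet the screen-failure condition. Nothing in the article keeps that patient in the analysis, calls the set modified ITT, or adds an all-randomized sensitivity analysis.

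**Step 2: the plan's own precision figure.** Inputs from Statistical analysis: 75 per arm, 40% against 25%, margin of error 12.4%.

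Margin = z × √[p1(1−p1)/n1 + p2(1−p2)/n2]

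With z = 1.645: 1.645 × √[(0.24 + 0.1875)/75] = 1.645 × 0.0755 = 12.4 points. This reproduces the plan.

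With 10% missing (67.5 per arm): 1.645 × √(0.4275/67.5) = 13.1 points, an increase of 0.7. This agrees with the plan's statement that the impact is below 1%. That reassurance concerns precision only and says nothing about bias from who is missing.

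**Step 3: exclusions on one side.** The article gives no expected number of untreated patients. I assume 8 of 75 in one arm (10.7%), all event-free, and all-randomized counts of 30/75 and 19/75, close to the planned rates. Margins use z = 1.645.

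| Set analysed | Control | Experimental | Difference (points) | Margin (points) |
|---|---|---|---|---|
| All randomized | 30/75 = 40.0% | 19/75 = 25.3% | -14.7 | 12.4 |
| 8 controls dropped | 30/67 = 44.8% | 19/75 = 25.3% | -19.4 | 13.0 |
| 8 experimental dropped | 30/75 = 40.0% | 19/67 = 28.4% | -11.6 | 13.0 |

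The all-randomized interval excludes zero (-14.7 + 12.4 = -2.3). With 8 experimental patients dropped it does not (-11.6 + 13.0 = +1.4).

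**Step 4: the same question from the treated rates.** Assume 40% and 25% among treated patients, so the treated-only difference is -15.0 points. The event rate among untreated patients is assumed to be 0% to 10%.

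- 5% untreated in both arms, no events in them: 0.95 × 25 − 0.95 × 40 = 23.75 − 38.0 = -14.25 points.
- 10% untreated in both arms, no events in them: 22.5 − 36.0 = -13.5 points.
- 10% untreated in control only: 25 − 36 = -11.0 with no events in them, 25 − 37 = -12.0 with a 10% event rate.
- 10% untreated in experimental only: 22.5 − 40 = -17.5 with no events in them, 23.5 − 40 = -16.5 with a 10% event rate.

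Balanced non-receipt matters little. One-sided non-receipt at 10% opens a gap of 1.5 to 4 points between the treated-only and all-randomized differences.

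**The case against.** The strongest reply is that the sentence speaks of patients, not randomized patients, and that a screen failure is ordinarily someone lost before randomization. The authors may have meant consented patients who never proceeded. That is possible, and the intent cannot be settled from the article. The wording, however, carries no such limit. It stands inside the ITT paragraph directly after the reference to random assignment, and its condition can be met after randomization.

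A second reply is that the effect will be small. Both arms receive radiotherapy, participants state willingness to comply, key treatment choices are declared before randomization, and the sample-size text expects minimal attrition. This stands as a limit on size. It does not remove the contradiction.

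A third reply is that a randomized-and-treated set is defensible for an acute radiotherapy toxicity endpoint. That is also fair, provided the set is named as such and the untreated patients are accounted for by arm.

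A reader might go further and infer several things the article does not support:

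- **Screen failures are replaced, so the 150 analysed differ from the 150 randomized.** Replacement is nowhere mentioned.
- **Patients know their allocation and leave because of it.** The physician must know the arm; the article does not say what patients are told.
- **Patients who start but do not finish radiotherapy are also removed.** They did receive radiotherapy, so this rule does not catch them.
- **The rule prescribes exclusion by arm.** It only permits exclusions that may turn out to differ.

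**Conclusion.** The point holds as a contradiction in the text: the analysis is called ITT, and the adjacent rule, as worded, allows randomized but untreated patients to be dropped. This does not depend on any calculation.

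Its size is unknown, because no untreated rate is given. Under the assumed one-sided loss of 8 event-free patients, a difference of -14.7 points becomes -19.4 or -11.6 depending on the arm. Losing event-free controls overstates the benefit, and losing event-free experimental patients understates it. With equal 5% non-receipt and no events among the untreated, the change is 0.75 points, minor beside a 12.4-point margin. A reader might conclude that the randomized comparison is broken for every endpoint. With minimal attrition expected, that is too strong. What can be said is that the analysis set is fixed badly and open to avoidable bias, under a label that would hide it.

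**What to change.** State that screen failure applies only before randomization, and that every randomized participant stays in the denominator of the assigned arm. Because the primary window is anchored on completing radiotherapy, give patients who never receive it an assessment window, for example to 3 months after the planned completion date. Report the set that received radiotherapy as a labelled sensitivity analysis.

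If the sponsor prefers a treated-only primary set, call it modified ITT, report the number untreated and the reasons by arm, and add an all-randomized sensitivity analysis.

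The cost is a wording change and light adverse event follow-up of a few untreated patients. The planned 150 and the 12.4-point margin at the planned rates are unchanged. The downside is slight dilution of the treatment contrast, and some events in untreated patients may come from other treatment they receive.

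### Stratifying the primary CMH test on all five balancing factors (48 cells for 150 patients) gives away power, and no test named delivers the absolute risk difference the trial is sized on

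*Protocol article*

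**What the plan says.** Under Design, allocation is dynamic: "A dynamic allocation procedure is used to assign participants in a 1:1 ratio". The factors to be balanced are given once: "Each arm will be balanced for risk group (intermediate/high), fractionation type (stereotactic body RT [SBRT] / non-SBRT), duration of androgen deprivation therapy", the last of these with levels "none/short-term/long-term), bladder filling (full/empty), and spacer use (yes/no".

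Under Statistical analysis, the aim is put in terms of estimation: "We will estimate the absolute difference in adverse event rate between tumor-focused radiotherapy and standard dose radiotherapy", by intention to treat. The sample size rests on the width of the interval for that difference: 75 per arm, 40% against 25%, margin of error 12.4%.

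The section then fixes the primary comparison: the arms "will be compared across the two randomized groups using a stratified Cochran–Mantel–Haenszel test with the stratification factors listed above". It adds: "We will also repeat the analysis using a non-stratified Fisher’s exact test". A multivariable logistic model with arm and all the listed covariates follows as a secondary analysis. No rule for pooling sparse cells and no subset of factors is stated.

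**The concern.** A CMH test compares the arms within each cell and adds up the results. A cell holding one arm only, or in which all patients or none have an event, contributes exactly zero. With about 3 patients per cell, many cells will be of this kind. Dynamic allocation over five factors usually balances each factor's margin rather than every cell, so it does little to prevent this.

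Two things are at stake. First, the named primary test has less power than the unstratified comparison on which the trial was sized, and that comparison has only moderate power itself. Second, the design is built on the precision of an absolute difference. The CMH and Fisher tests give p-values, and the logistic model gives effects on the odds scale. The 12.4-point precision therefore belongs to an analysis that the list of analyses does not name.

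**Working it through.** **Inputs.** From Design: factor levels 2, 2, 3, 2, 2 and 1:1 dynamic allocation. From Statistical analysis: 75 per arm, 40% against 25%, margin 12.4%. Factor prevalences are not in the article, so they are assumed and varied.

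**1. The plan's own figure.** SE = √(0.40·0.60/75 + 0.25·0.75/75) = √0.0057 = 0.0755. Margin = 1.645 × 0.0755 = 12.4 points. This reproduces the stated value, so that value is the unstratified Wald margin at z = 1.645. (z = 1.96 would give 14.8.) With 10% missing: 12.42/√0.9 = 13.1, a rise of 0.7, as the plan says. The power of the unstratified comparison is 63% at one-sided 5% and 50% at two-sided 5%.

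**2. Number of cells.** 2·2·3·2·2 = 48, and 150/48 = 3.1 patients per cell, about 1.6 per arm.

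**3. Information kept.** Measure information as the sum over cells of n₁n₀/n. Unstratified, this is 75·75/150 = 37.5. If 75:75 allocation ignores the cells, its expected value with K occupied cells is 37.5 × (150 − K)/149. The fraction kept is therefore (150 − K)/149: each occupied cell costs about one patient's worth of information. With 48 equally likely cells, K = 48 × (1 − (47/48)^150) = 46.

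**4. Simulation.** There were 3,000 trials per scenario, using CMH without continuity correction and four assumed factor mixes. Results for simple 75:75 allocation with non-prognostic factors:

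| Assumed mix | K | (150 − K)/149 | Kept (simulated) | Patients in one-arm cells | Uninformative patients | Margin of a 48-cell risk difference | One-sided power, CMH / unstratified |
|---|---|---|---|---|---|---|---|
| Equal | 45.9 | 0.70 | 0.70 | 30.8 | 57.2 | 14.9 | 49.0% / 62.4% |
| Moderate | 42.8 | 0.72 | 0.72 | 28.0 | 48.9 | 14.6 | 51.0% / 63.0% |
| Skewed | 33.9 | 0.78 | 0.78 | 21.6 | 33.8 | 14.1 | 53.8% / 63.5% |
| Very skewed | 23.0 | 0.85 | 0.85 | 14.0 | 20.8 | 13.5 | 57.9% / 62.7% |

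Minimisation helps slightly, keeping 0.72 to 0.88. Letting the factors be prognostic does not remove the loss. Over all sixteen combinations the loss of one-sided power was 4.4 to 13.4 points, with a simulation error of about 1 point in each power figure. A separate set of runs gave 48–56% against 62–65%. I summarise this as about 5 to 14 points. Two-sided 5% power was 37–46% against about 49–51%.

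**5. Check by normal approximation.** 0.15/0.0755 = 1.987. With 70% of the information kept: 1.987·√0.70 − 1.645 = 0.017, power 51%. With 88% kept: 1.987·√0.88 − 1.645 = 0.219, power 59%. With all of it: 0.342, power 63%.

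**6. Fewer cells.** With two binary factors (4 cells), (150 − 4)/149 = 0.98. Simulation also gives 98% kept, a margin of about 12.5 points and one-sided power of 61–63%.

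**The case against.** The strongest reply has four parts.

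- **Validity.** A reader might infer that 48 sparse cells make the test invalid or inflate its type I error. They do not. CMH is designed for many small strata, and the cost is efficiency only. This stands.
- **The risk difference.** A reader might also infer that the announced estimate has no place in the plan. That goes too far. The section commits to estimating it by intention to treat with an interval, and the 12.4-point figure shows which interval was used for planning. Reporting a risk difference beside a CMH p-value is common practice, and formula details may sit in an analysis plan that is not shown. What remains is narrower: the tests named for the primary comparison do not deliver that quantity as specified.
- **Size.** The larger losses come from independent, evenly spread factors. If ADT duration and fractionation go with risk group, fewer cells are occupied. Simulation under such assumed correlations gave 23–30 occupied cells, 20–30 uninformative patients, and power of 55–58% against 61–63%. This supports the lower end of the range but leaves a real loss.
- **Partial cover.** The Fisher test uses every patient, and the logistic model is close to one of the remedies below. But both are supporting analyses, and neither gives a risk difference as written.

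**Conclusion.** The point holds as a matter of efficiency and of fit with the sizing, and it should be fixed. The 48 cells follow directly from the text. The size of the loss depends on factor mixes that the article does not give. Over those tried, roughly 20 to 60 patients are uninformative, 70–88% of the information is kept, and one-sided power falls by about 5 to 14 points from about 63%. In terms of information this equals losing 12–30% of the patients, more than the 10% attrition the plan allows for.

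The documents do not support calling this a fatal flaw. The test is valid, the risk difference is promised, and an unstratified test is reported alongside. That power is only about 63% even without stratification is a separate sample-size matter and does not make this point more serious.

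**What to change.** In the Statistical analysis section, name one estimator of the absolute risk difference as the primary analysis, with its interval at the level used in the sample-size paragraph (z = 1.645). Either of these would do:

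- **A standardised risk difference** from the logistic model already planned, with arm and the five factors as main effects. That is 1 + 1 + 1 + 2 + 1 + 1 = 7 coefficients besides the intercept, against 75·0.40 + 75·0.25 ≈ 49 expected events.
- **A Mantel–Haenszel risk difference with its CMH test** over a small prespecified subset of factors, for example two binary ones (4 cells). The article gives no ground for preferring a particular pair, so the sponsor should choose and justify it before looking at outcomes by arm.

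Keep the unstratified test as a sensitivity analysis. The change is to wording only and needs no new data. The price is reliance on a main-effects working model in the first option, or adjustment for fewer factors in the second.

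### Bootstrap intervals for the seven-slope logistic model cost little in the whole trial but become uninterpretable when the model is repeated in subgroups of about 50 patients or fewer

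*Protocol article*

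**What the plan says.** The Statistical analysis section of the Protocol article sets out, as a secondary analysis, a multivariable logistic model for acute grade ≥2 GU or GI events, with "independent variables to include randomization group and all covariates listed above". I read the covariates as the balancing factors in the Design section, which begins "Each arm will be balanced for risk group (intermediate/high), fractionation type" and goes on to ADT duration (three levels), bladder filling and spacer use. The interval method is fixed: "This will allow us to estimate the effects of each variable, with bootstrap 95% confidence intervals".

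The section continues: "The primary and secondary analyses above will be repeated in the following subgroups", naming race/ethnicity and age below 65 versus 65 and over. It adds subgroup analyses within the levels of the balancing factors. The article gives no bootstrap type, no rule for resamples that cannot be fitted and no subgroup sizes.

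**The concern.** A bootstrap refits the model to samples drawn with replacement. When there are few events per coefficient, some resamples are separated: a covariate pattern predicts the outcome perfectly and the maximum likelihood estimate runs off to infinity. A 95% percentile interval puts 2.5% in each tail. Once more than 2.5% of resamples send a coefficient off in one direction, that limit depends on the stopping rule of the software and not on the data.

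The plan promises an interval for every variable, so divergence in any slope matters, not only in the arm term. At stake are the covariate-adjusted subgroup results for the primary endpoint. They could be printed with limits that look like estimates and are not.

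**Working it through.** **Inputs from the article (Design; Statistical analysis).** Rates: "If we assume acute adverse events are reduced from 40% to 25% (absolute rate difference of −15" points). Size: "a sample size of 150 participants (75 in each arm"). Five balancing factors, one with three levels.

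**The plan's own figure.** The article gives no figure for the logistic model. Its stated precision, "with 12.4% margin of error", concerns the risk difference: z × √(0.40×0.60/75 + 0.25×0.75/75) = z × 0.0755. With z = 1.645 this is 12.42 points, which agrees. So the planning inputs are read correctly.

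**Events per slope.**
- Slopes: arm 1 + risk 1 + fractionation 1 + ADT 2 + bladder 1 + spacer 1 = 7.
- Expected events: 75×0.40 + 75×0.25 = 48.75, and 48.75/7 = 7.0 per slope.
- The overall rate is 48.75/150 = 32.5%. A subgroup of 75 has about 24 events (3.5 per slope), one of 50 about 16 (2.3) and one of 30 about 10 (1.4).

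**Simulation assumptions.** The article gives no factor mix, covariate effects or subgroup sizes. I assumed a balanced and an uneven factor mix, covariate log odds ratios of ±0.2, and 500-1000 resamples per data set. There were 1000-1500 simulated trials at n=150 and about 300 data sets at each smaller size. Separation was flagged mainly by a coefficient above 8 in absolute value.

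**Whole trial (n=150), arm log odds ratio, balanced / uneven mix.**

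| Interval | Median width | Coverage |
|---|---|---|
| Wald | 1.49 / 1.48 | 94.1% / 92.4% |
| Profile likelihood | 1.49 / 1.49 | 93.7% / 92.0% |
| Percentile bootstrap | 1.66 / 1.66 | 93.5% / 92.0% |
| BCa bootstrap | 1.64 / 1.64 | 96.7% / 95.8% |

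The Monte Carlo standard error of coverage is 0.6-0.7 points. The percentile interval is 11-12% wider than Wald (1.659/1.487 = 1.12) and BCa is 10% wider. Only 0.2-1% of resamples were separated.

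**Subgroups, full model, balanced / uneven mix.** Data sets already separated before resampling appear only in the last column.

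| Patients | Resamples separated or not estimable | Data sets with a divergent percentile limit for at least one slope | Original data already separated |
|---|---|---|---|
| 100 | 2% / 7% | 15% / 43% | 0.3% / 1.3% |
| 75 | 6% / 16% | 45% / 78% | 1-4% |
| 50 | 25% / 41% | 97% / 100% | 4-16% |
| 30 | 70% / 79% | 100% | 33-54% |

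For the arm term alone, a limit diverged in about 3% of data sets at 75, about 50% at 50 and 100% at 30. In the uneven mix at n=50, the bootstrap-SE interval had median width 18.56 against 2.87 for Wald. That type is therefore no refuge in small subgroups.

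**Are such sizes plausible?** Any split of 150 into three or more groups leaves one with at most 150/3 = 50. This applies to the three ADT levels and to race/ethnicity if three or more categories are used. Within a factor level that factor drops out, leaving 6 slopes, or 5 within an ADT level, which eases the problem slightly.

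**Penalised alternative.** In separate simulations of 120-150 data sets per size, Firth estimates were finite in every data set at n=150, 60 and 40, with coverage of 94-97%. With 150 data sets the Monte Carlo standard error is √(0.95×0.05/150) = 1.8 points.

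**The case against.** **Bootstrap type.** A reader might infer that bootstrap intervals in general are needlessly wide here. The article does not support that, because it names no type. At n=150 the percentile interval gains no coverage, but BCa and bootstrap-SE intervals reached about 96-97% where Wald gave 92-94%. Some of the extra width may buy coverage.

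**Loss of information.** A reader might also square the width ratio and say that about a fifth of the patients are discarded (1 − 1/1.11² = 0.19). That is a statement about width only. No data are lost and the point estimate does not change.

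**Subgroup size.** Nor do the documents support saying that most resamples fail in the race/ethnicity and age subgroups generally. At 100 patients few are separated, and at 75 the arm limit is rarely affected. Nothing shows that the age groups or the largest race/ethnicity category will be small.

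**Diagnosis.** In the smallest subgroups ordinary maximum likelihood fails too, so changing only the interval would not cure them. This stands, and it is why the fix changes the fit as well.

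**Detail left to another document.** Bootstrap type and handling of failed resamples may be in a plan not shown, and their absence here is no fault. But the article does fix the bootstrap, the full covariate list and the repetition in subgroups. That combination, followed as written, is what fails.

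**Importance.** The model is secondary. The Cochran-Mantel-Haenszel and Fisher tests do not use these intervals. This stands and limits the weight of the point.

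**Conclusion.** The point holds for small subgroups and is minor overall. In the whole trial the stated method works: a percentile bootstrap costs 11-12% in width of the arm interval with no gain in coverage, and other types may do better. In subgroups of about 50 or fewer, the full model gives at least one divergent limit in nearly every simulated data set, and a divergent arm limit in about half at 50 and in all at 30. Such limits cannot be interpreted.

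The counts of 7 slopes and about 49 events follow from the article. The separation shares rest on assumed factor mixes, covariate effects and subgroup sizes. The sentence on the balancing-factor subgroups does not say outright that the logistic model is refitted there; for race/ethnicity and age the text does.

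**What to change.** In the sentence on the logistic model, replace the bootstrap clause by Firth-penalised logistic regression with profile penalised-likelihood 95% confidence intervals. Apply this at least in the subgroup analyses and preferably overall, so that one method is used throughout.

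Add a pre-specified minimum event count below which a subgroup model contains arm only. The checks of the penalised fit reach down to 40 patients, about 40×0.325 = 13 events. A lower threshold would need its own simulation with the factor mix the sponsor expects.

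The cost is a sentence or two and a standard software option. The penalty shrinks estimates slightly toward zero, which should be stated when the results are reported. The primary analysis and the sample size stay as they are. The change should be made before outcome data are seen.

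### Subgroups are to be examined by repeating the whole-trial tests inside them, with no interaction test stated; this cannot show whether the effect differs and often gives discordant p-values

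*Protocol article*

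**What the plan says.** The Statistical analysis section compares the primary endpoint between arms "using a stratified Cochran–Mantel–Haenszel test with the stratification factors listed above", repeats this with an unstratified Fisher's exact test, and then fits a logistic model with "independent variables to include randomization group and all covariates listed above" and bootstrap 95% intervals. No treatment-by-factor term is listed.

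On subgroups it then says "The primary and secondary analyses above will be repeated in the following subgroups" and names two: self-reported race/ethnicity, and age below 65 versus 65 or over. It continues: "This is in addition to subgroup analyses within the stratification groupings for randomization". For those groupings no method is named.

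The Design section lists the five factors: risk group (2 levels), fractionation (2), ADT duration (3), bladder filling (2) and spacer use (2).

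**The concern.** The only subgroup method the article fixes is re-running whole-trial analyses inside each level. A significant result in one level beside a non-significant one in another is not evidence that the effect differs. With small levels, that pattern is what chance produces when the effect is uniform. Whether it differs is answered by comparing the levels directly, with an interaction.

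The repeated analyses were also sized, at best, for 150 patients. A CMH test over the cross-classified factors and a model with every covariate have little to work with in a subgroup.

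At stake is the reading of the secondary results. The article says the trial will inform a phase III trial and stresses relevance to most patients having definitive RT. A chance pattern by age, ethnicity or technique would sit awkwardly beside that aim. The primary analysis is not affected.

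**Working it through.** **Inputs from the article.** 75 patients per arm; event rates 40% and 25%; factor levels as in the Design section. **Assumed:** race/ethnicity categories k = 4 (range 2–6), subgroup sizes (equal and unequal splits both tried), independence between factors, nominal two-sided 0.05.

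**1. The plan's own figure.** SE = √[(0.40×0.60 + 0.25×0.75)/75] = √(0.4275/75) = 0.0755. Then 1.645 × 0.0755 = 12.4 points, the stated margin of error. The two-sided 95% half-width is 1.96 × 0.0755 = 14.8 points.

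**2. Number of subgroups.** The randomization factors give 2+2+3+2+2 = 11 levels and age gives 2, so the total is 13 + k: 17 if k = 4, and 15–19 for k = 2–6.

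**3. One half-size subgroup (37.5 per arm).** SE = √(0.4275/37.5) = 0.107, so the 95% half-width is 20.9 points. Power at 40% versus 25% is 28%, against 50% in the whole trial. It is 20% at 25 per arm and 10% at 10 per arm.

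**4. Hand check for one 50:50 factor, uniform effect.** The two levels share no patients, so P(one significant, the other not) = 2 × 0.28 × 0.72 = 0.40. A valid interaction test would be falsely positive 5% of the time.

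**5. All factors together.** The factors cut the same 150 patients, so the subgroups overlap and simulation is needed (2,000–3,000 trials per scenario, no true interaction). Discordant means at least one factor has one level significant and another not.

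| Scenario | Chi-square | Fisher | CMH |
|---|---|---|---|
| Uniform 40% vs 25%, 17 subgroups: discordant | 82–83% | 76–77% | 70–73% |
| Same, age and race/ethnicity only: discordant | 64% | – | 39–41% |
| No effect, 17 subgroups: at least one significant | 44–46% | 33–34% | 37–42% |

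With 15 subgroups (k = 2), discordance under the design effect is 73–80% (Fisher to chi-square). With no effect, discordance for age and race/ethnicity alone is 15–25%. Treating 17 subgroups as independent would give 1 − 0.95^17 = 58% in the last row, which is too high because they overlap.

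**6. Sparsity.** The factors cross to 2×2×3×2×2 = 48 strata. That is 150/48 = 3.1 patients per stratum in the whole trial and 75/48 = 1.6 in a half-size subgroup. CMH uses only strata that contain both arms and both outcomes. Under assumed factor frequencies, such strata hold 62–73% of patients in the whole trial, 35–53% in a 75-patient subgroup and 14–27% in a 30-patient one. The logistic model needs at least 7 terms (arm, risk, fractionation, two for ADT, bladder, spacer). At the pooled rate of 32.5%, 75 patients give about 24 events, or 3.5 per term; 20 patients give 6.5 events, fewer than 1 per term.

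**7. With interactions instead.** Seven factors give seven tests. The chance of any false positive is 1 − 0.95^7 = 30% (simulated 27–31%), or about 5–6% with a Bonferroni adjustment, with or without an overall effect. For a 50:50 factor, the SE of the difference between two risk differences is √2 × 0.107 = 0.151, a 95% half-width of 29.6 points. A true 15-point interaction would therefore be detected with power of about Φ(0.15/0.151 − 1.96) ≈ 17%.

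**The case against.** The strongest reply is that this is silence in a condensed article. Interaction tests, multiplicity rules and an exploratory label usually sit in the analysis plan, which is not shown. That stands as far as it goes, and a reader should not infer that the sponsor has chosen separate tests in place of interactions: none is named, but none is excluded. What remains is the part the article does fix, namely repeating the tests and the model within subgroups.

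Four other inferences are tempting and not supported:

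- **That the full repeat applies to all five randomization factors.** It is explicit only for race/ethnicity and age. For the other 11 levels the text promises subgroup analyses and no method, so the 70–80% figure assumes they are handled in the same way.
- **That there are 17 subgroups.** That needs four race/ethnicity categories; the article supports 13 + k.
- **That spurious findings are the usual result whatever the truth.** With no effect, the chance of any significant subgroup is below one half for every test. For age and race/ethnicity alone, discordance with CMH is about 40% even under the design effect.
- **That discordant p-values will be declared subgroup effects or used to choose the phase III population.** Nothing says so. The section describes an estimation approach, and the Summary ties phase III to the overall hypothesis.

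It can also be said that a 48-stratum CMH test is already sparse in the whole trial. That is true and is a separate matter; subgrouping makes it worse.

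**Conclusion.** The point holds in limited form. The named subgroup method cannot answer whether the effect varies, and at this sample size it often yields patterns that look as if it does. Under the plan's own uniform effect, discordant significance appears in about 70–80% of trials over all factors (up to 83% with chi-square, a test the plan does not name), and in about 40% for age and race/ethnicity alone with CMH. With no effect, at least one subgroup is significant in about 37–46% of trials by CMH or chi-square and 33–34% by Fisher. The all-factor figures rest on k = 4, independent factors, assumed subgroup sizes, and the same tests being used in the randomization groupings. Discordance becomes a false conclusion only if it is read as one. This is a cheap improvement to a secondary analysis, not a flaw in the primary comparison.

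**What to change.** Replace the repetition within subgroups by a statement that heterogeneity will be assessed with one treatment-by-factor interaction per factor, either in the logistic model already planned or as a difference in risk differences. Show each subgroup's risk difference with a 95% interval, drop the repeated within-subgroup tests and full-covariate models, and label all of it exploratory. State the race/ethnicity categories, and say that the same approach covers the randomization factors.

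The cost is wording, with less analysis to run. There are two limits to state openly. Interaction power is low at 150 patients, so most results will be inconclusive. And seven unadjusted interaction tests still carry about a 30% chance of at least one false positive, so either adjust (about 5% with Bonferroni) or report that chance beside the results.
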